#### Qualitative analysis of interviews

For aims 1 and 2, we will follow best practices for conventional content analysis [99], using Microsoft Excel and NVivo qualitative software to organize and analyze the new interview transcripts. The first two authors will first read and sort sections of the transcripts into common themes. We will use the previous project’s themes as a starting point [32], but allow for iterative refinement through the identification of emergent themes and comparison to concepts represented in EPIS. Once 50% of interview data are collected for a wave, we will develop a codebook with theme descriptions, definitional criteria, and exemplars [100], then train research assistants to code the remaining transcripts. After fully coding 10% of the interviews, we will review the coding and discuss discrepancies to finalize the codebook. Interviewing staff will also provide input into coding. If our codebook has major changes from the previous project, we will re-code prior qualitative data with the new codes.

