	Organization-reported barriers/ facilitators of A-CRA sustainment	Clinicians, supervisors^b^			
	State agency-reported barriers/ facilitators of A-CRA sustainment	State behavioral health agency administrators			
	Impact of COVID-19 on A-CRA sustainment	Clinicians, supervisors, state behavioral health agency administrators			
Web survey (all waves)			30 min	$25	Aims 2a, 2b, 3
	*A-CRA clinician knowledge	Clinicians^b^			
	Sustainment capacities (PSAT) [67]	Clinicians, supervisors^b^			
	External support [65]	Supervisors^b^			
	Leadership support (ILS [66])	Clinicians^b^			
Document review	A-CRA sustainment-related documents	State behavioral health agency administrators	as needed	n/a	Aims 2a, 2b, 3

*A-CRA* Adolescent Community Reinforcement Approach, *ILS* Implementation Leadership Scale, *PSAT* Program Sustainability Assessment Tool

^*^An element that is used to calculate the 10-element A-CRA sustainment outcome measure [68]

^a^See Fig. 1 for details of the project aims and how they relate to each other

^b^Data collected from organization-focused grantees in the previous project will be included in the analysis

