#### Previously collected interviews

As noted previously, we collected semi-structured interviews from 169 clinicians and supervisors at organization-focused grantee organizations [32, 34]. The interviews were collected across three waves up to 5 years post-funding. These data will be combined with interview data from state-focused grantees for the planned analyses. As much as possible, the interview protocols for the current project were adapted from those used in our prior work, to ensure comparability of findings. We also grounded the protocols in the EPIS framework, to ensure we consistently ask about multi-level influences on A-CRA outcomes while distinguishing between implementation and sustainment phases.

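### Prior organization-focused interviews are re-coded only after major codebook changes, so a code added or altered below that threshold would be applied to state-focused interviews alone

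*Protocol article*

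**What the plan says.** Under Qualitative analysis of interviews, the content analysis for Aims 1 and 2 uses software to "organize and analyze the new interview transcripts". It starts from the earlier project's themes but will "allow for iterative refinement through the identification of emergent themes and comparison to concepts represented in EPIS". On timing, the article says: "Once 50% of interview data are collected for a wave, we will develop a codebook". The prior material is handled by one conditional sentence: "If our codebook has major changes from the previous project, we will re-code prior qualitative data with the new codes".

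The prior interviews come from 169 clinicians and supervisors at organization-focused grantees. The section Previously collected interviews says of them: "These data will be combined with interview data from state-focused grantees for the planned analyses". Tables 2 and 3 list the data used to compare penetration and sustainment between grant types. In both, the row for organization-reported barriers and facilitators carries footnote b: "Data collected from organization-focused grantees in the previous project will be included in the analysis".

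**The concern.** The codebook can grow or be refined from what state-focused respondents say, while the organization-focused transcripts keep their earlier codes unless the change is judged large enough. Any resulting difference in coding coincides exactly with grant type, which is the exposure under study. A reader who saw a theme in one group and not in the other could not tell a real difference in experience from a code that was never applied to the second group.

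At stake is the explanatory strand of the study. The Analysis plan uses qualitative data to deepen the reading of the Aim 1 and Aim 2 results. The Sensitivity analyses section turns to them to understand why a grant effect shrinks once time is controlled. Under Policy implications, findings from those aims guide the focus groups.

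**Working it through.** No arithmetic applies. The rule concerns coding, and the article gives no figure to reproduce. The check sets the relevant statements side by side.

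1. **Where new codes come from.** The described theme development is on the new, state-focused transcripts. The older transcripts supply the starting themes, but no fresh reading of them for new themes is described unless re-coding is triggered.
2. **How often the codebook can change.** Table 1 plans four waves, and the codebook sentence refers to a wave. If it is meant to apply at each wave, refinement can recur. If it is meant once, there is a single occasion. The point holds either way.
3. **Whether the two sets meet in one analysis.** They do. Previously collected interviews says that they are combined, and footnote b puts the prior data behind the organization-reported barrier and facilitator rows of both tables. The state-agency-reported rows and the COVID-19 row carry no footnote b, so the article claims no comparator for them.
4. **What the re-coding rule then implies.** There are two branches:
   - The change is judged major. The prior transcripts are re-coded with the new codes, and a new theme can be found in either group. There is no asymmetry.
   - The change is judged not major. The prior transcripts keep the old codes. A code added from the new transcripts has no counterpart in the older set, and a split or redefined code has a different meaning there. A comparison on that code is not like with like.
5. **Which results use these codes.** Penetration comes from the training organization's certification records. Sustainment comes from the 10-element score. The Mechanisms section says that all moderator and mediator variables come from the web surveys. None of these draws on thematic codes, so the second branch reaches only the qualitative comparison and the interpretation built on it.

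**The case against.** The strongest reply is that the quoted sentence is itself a safeguard: the authors foresaw codebook drift and committed to re-coding when it is substantial. A newly added theme may be just what they mean by a major change. The shared starting themes limit drift, and so do the interview guides, since as far as possible "the interview protocols for the current project were adapted from those used in our prior work, to ensure comparability of findings". A journal article may also leave the working definition of a coding threshold to the codebook or full protocol.

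Most of this stands, and it rules out several stronger readings that a reader might be tempted to draw:

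- *Every emergent theme is missing from the comparator.* This does not follow, because a major change does trigger re-coding.
- *The asymmetry favours the hypothesis that state-focused grants do better.* The documents do not support a direction. A barrier coded only in state-focused interviews would make those grants look worse.
- *State infrastructure themes would be the clearest artefact.* Infrastructure is asked about in the state administrators' interviews, and the state-agency rows claim no comparator. Building it was also part of the state-focused grants by design, so its appearing in that group alone could be largely real.
- *The distortion equals the full frequency of the theme in the state-focused group.* The article specifies no between-grant comparison of theme frequencies, and does not say that an unapplied code would be reported as zero.

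The reply does not remove the narrow point. The missing definition is not the finding; the finding is that re-coding depends on the size of the overall change. Unless the definition takes in every added, split or redefined code, some changed codes will exist in one group only.

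**Conclusion.** The point holds in a limited form and is a low-priority improvement. Under the stated rule, a code changed below the major-change threshold is applied to state-focused interviews only, and its absence among organization-focused grantees would not be evidence of a difference. How many codes this affects is unknown, and so is the direction.

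The conclusion rests on two assumptions: that at least one code is added, split or redefined without being judged a major change, and that the study team then draws a between-grant contrast on that code. If a fuller document defines any such change as major, the problem disappears. The planned quantitative tests for Aims 1 and 2 are unaffected in any case.

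**What to change.** Replace the major-change trigger with a rule for each code. Before any between-grant comparison of themes, apply every code that was added, split or redefined relative to the earlier project's codebook to the prior transcripts. Where this is not done, or where the topic could not have arisen in the earlier interviews (COVID-19 is the obvious case), report the code for state-focused grantees only and draw no comparison.

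The cost is research-assistant time for targeted re-coding of existing transcripts, limited to the changed codes and using staff and software that the plan already includes. The fallback of reporting without comparison needs no re-coding. Its price is that the contrast on that theme is given up.

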#### Quantitative data analysis

We will integrate the data collected in this project with our prior data [33, 34, 48]. To compare state-focused vs. organization-focused grants, we will fit hierarchical models for penetration outcomes (aim 1) and longitudinal pattern-mixture models [101, 102] for sustainment outcomes (aim 2). Variables in the model come from two levels, state and organization, with ratings from multiple respondents averaged to the organization level (as in the previous project). In aim 2, each organization will have up to four repeated measurements, allowing us to fit organization-specific trajectories. Longitudinal pattern-mixture models do not require fully synchronized measurements across organizations, which is suitable for our analyses. We will have missing data at some measurement points due to nonresponse and the timing of data collection (see Table 1), so we will apply multiple imputation [103] and data reweighting [104] to handle nonresponse. If organizations differ significantly on observable characteristics and baseline outcomes, the model fitting process will use propensity scores [105] to adjust for covariate balancing. These models can be readily fit in the general statistical software package SAS 9 PROC MIXED. After fitting all models, we will apply the step-up method [106] to adjust for multiple comparisons and maintain a type I error rate <0.05 for each aim. For analyses of mechanisms, we will examine moderators by adding interaction terms to the models and will use structural equation models to examine indirect and direct mediation effects; for aim 2, the moderator and mediator variables are time-varying. Additional file 4 presents detailed equations for each analysis in aims 1 and 2.

We hypothesize that treatment organizations implementing A-CRA under state-focused grants will have higher penetration rates compared to organization-focused grantees, with differences between grant types moderated by external support and leadership quality. Similarly, we predict that state-focused grants will show greater A-CRA sustainment by treatment organizations across 5 years post-funding, with moderation by leadership quality and sustainment capacity mediation by changes in external support and funding stability over time.

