**Method:**

We will employ a longitudinal, mixed-method (i.e., web surveys, semi-structured interviews, document review, focus groups, administrative data), quasi-experimental design to compare the grant types’ outcomes and examine theoretically informed mediators and moderators. Aim 1 will examine the proportion of eligible clinicians certified in A-CRA with adequate fidelity levels (i.e., penetration outcomes) at the end of grant funding. Aim 2 will examine the sustainment of A-CRA up to 5 years post-funding, using a 10-element composite measure of treatment delivery and supervision activities. We will integrate the new data collected from state-focused grant recipients (~85 organizations in 19 states) with previously collected data from organization-focused grant recipients (Hunter et al., Implement Sci 9:104, 2014) (82 organizations in 26 states) for analysis. We will also use sensitivity analyses to characterize the effects of observed and unobserved secular trends in our quasi-experimental design. Finally, aim 3 will use comparative case study methods (integrating diverse quantitative and qualitative measures) to identify and disseminate policy implications about the roles of state- and organization-focused federal grants in efforts to promote adolescent SUD EBP implementation and sustainment.

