## Method

### Research design

Aims 1 and 2 use a longitudinal, natural experiment design to compare A-CRA penetration and sustainment for state-focused grants (new data collection) versus organization-focused grants (collected previously [48]). Given that this is a natural experiment wherein we did not assign participants to grant types, we will conduct a sensitivity analysis that characterizes the influence of observed and unobserved secular trends on our estimates of grant type effects. Aim 3 will use a comparative case study design [55, 56] to identify policy implications for federal SUD service grants. Across aims, qualitative and quantitative data will be collected concurrently within a mixed-method approach [57].

In this protocol, we followed the Standards for Reporting Implementation Studies [58] (StaRI; see Additional file 1) for describing our project. All described procedures were reviewed and approved by the RAND Corporation IRB (Protocol #2020-N0887).

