### Project context

As noted earlier, SAMHSA has used both organization-focused and state-focused discretionary grant strategies to fund EBP implementation (including A-CRA) for adolescent SUD. All grants were administered by SAMHSA’s Center for Substance Abuse Treatment [59], whose primary role was to provide funding, oversight, and national leadership to grantee organizations and states/territories/tribal entities (hereafter, “states”). SAMHSA funded (i) four cohorts of organization-focused grantees, awarded 2006–2010, across 26 states followed by (ii) four cohorts of state-focused grantees, awarded 2012–2017, across 22 states. Eight states had recipients of both grant mechanisms, so overall, 40 states were represented across cohorts.

In both initiatives, SAMHSA partnered with Chestnut Health Systems (CHS; an organization that conducts A-CRA training and research) to provide training and certification for A-CRA clinicians and supervisors. CHS provided a standardized, 2.5-day training for all organization-focused grantees and most clinicians in state-focused grantees’ states—although some received training from certified A-CRA supervisors. In every case, CHS still oversaw A-CRA clinician and supervisor certification. Certification activities required each trainee to demonstrate competency in delivering A-CRA treatment and/or supervision procedures, depending on their role. Specifically, clinicians and supervisors participated in twice monthly, group-format coaching calls with CHS expert consultants; they also submitted audio-recorded A-CRA therapy or supervision sessions, respectively, and their consultant provided numeric ratings and written feedback [60–62]. Typically, the certification process lasted from 6 months to a year.

Next, we describe the two grant types in more detail. We follow recommendations for specifying implementation strategies in terms of actors, actions, action targets, temporality, dose, outcomes, and justification [27, 36].

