#### Treatment organizations

In our previous project, we collected semi-structured interview and survey data from 169 clinicians and supervisors at 78 treatment organizations (across 27 states) that received SAMHSA organization-focused grants [33, 34]. The current project involves collecting similar data from treatment organizations that received support from their state agency to implement A-CRA as part of a state-focused grant, including the dissemination sites and any other organizations that implemented A-CRA. To be included in the current project, organizations must be located in a state where less than 5 years have passed since their state-focused grant ended.

Given the larger scope of state-focused grants, we will not collect data from every treatment organization involved (across the 19 eligible states, CHS records indicate that staff from 282 organizations received A-CRA training). Instead, we used a three-step sampling procedure to select up to five organizations per state from which data will be collected; this approach kept data collection feasible and ensured that organizations from highly successful states were not overrepresented. First, we identified five organizations (in four states) that received training through a state-focused grant while their organization-focused grant was still active, and excluded them due to the extent of confounding. Second, we selected up to three dissemination sites to ensure we included some organizations targeted directly by state-focused grants without overrepresenting the organizations most likely to implement A-CRA successfully; we randomly selected three dissemination sites if a state had more. Third, we randomly selected from the remaining treatment organizations in each state until we reached a maximum of five per state. These procedures selected 91 organizations (*M* = 4.78 per state) from which we will recruit. Chi-squared tests using CHS administrative data indicated that clinicians and supervisors from the selected organizations were no more or less likely to be A-CRA certified (*χ*^2^_(1)_ = 3.416, *p* = .065) or to have left the organization (χ^2^_(1)_ = 2.480, *p* = .115) than those not selected.

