### Data sources and collection procedures

We will collect four waves of quantitative and qualitative data from state-focused grantees, to be combined with administrative records from CHS and previously collected data from organization-focused grantees. Table 1 details the planned data collection schedule. In each wave, we will collect data (semi-structured interviews, surveys, document review) from state agency representatives and clinicians/supervisors. Treatment organizations that report no longer delivering A-CRA will complete the ongoing wave of data collection, but will only participate in subsequent waves if they begin delivering A-CRA again and thus have new information to share (we will verify at the beginning of each wave). Focus groups with state and federal agency administrators will take place in the final year and so are not included in Table 1.

**Table 1 Tab1:** Waves of planned data collection for state-focused grant cohorts

Grant cohort (years)	Target # of organizations	Expected # of respondents	Data collection waves: years since funding ended			
			Wave 1 (2021–2022)	Wave 2 (2022–2023)	Wave 3 (2023–2024)	Wave 4 (2024–2025)
(1) 2013–2017	7 states 37 organizations	7 state agency administrators 33 clinicians 47 supervisors	4 years Post-funding	^a^5 years post-funding	*NA*	*NA*
(2) 2012–2018	7 states 33 organizations	7 state agency administrators 29 clinicians 42 supervisors	3 years Post-funding	^a^4 years post-funding	^a^5 years Post-funding	*NA*
(3) 2017–2021	5 states 21 organizations	5 state agency administrators 19 clinicians 27 supervisors	0 years Post-funding	^a^1 year post-funding	^a^2 years Post-funding	^a^3 years Post-funding

In each data collection wave, we will collect semi-structured interviews from all eligible participants, web-based surveys from eligible clinicians and supervisors, and grant-related documents for review from eligible state agency administrators

*NA* not applicable (i.e., data are not collected because the data collection wave falls more than five years post-funding)

^a^ Treatment organizations that reported not sustaining the Adolescent Community Reinforcement Approach (A-CRA) in the previous wave will not be eligible unless they report having restarted A-CRA delivery since the previous wave

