#### Statistical power

For aim 1, under regular settings (power>80%, 2-sided *p*-value<.05), we can detect a medium effect size of 0.46 times standard deviation (*SD*) on penetration when the covariates have no effect, and a medium effect size of 0.40 times *SD* when the covariates explain 20% of the variance in penetration. The power for moderation analysis is weaker and more difficult to quantify; in a simplified setting of high versus low values, we can detect a large moderation effect size of 0.89 times *SD*.

Under the same settings for aim 2, if we suppose that across all patterns each treatment organization can provide two measurements over time, on average, and assume an intra-class correlation no greater than 0.40, we can detect a small standardized effect size of 0.34 times *SD*. Based on guidelines for mediation analysis [107], we can detect a moderately small mediation relationship (i.e., standardized *μ*^(0)^=0.26) by most methods drawing inference for the indirect effect, when the intra-class correlation is no bigger than 0.50. In a simplified setting of high vs. low values in a moderator, we can detect a medium moderation effect size of 0.69 times *SD*.

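### Propensity adjustment in a non-randomised comparison should not wait for a significance test, nor be triggered by outcomes measured only after the grants began

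*Protocol article*

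**What the plan says.** The Research design section calls the study a natural experiment in which "we did not assign participants to grant types". The Project context section gives award periods that do not overlap: "four cohorts of organization-focused grantees, awarded 2006–2010, across 26 states", then state-focused awards from 2012 to 2017.

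For confounding between organizations, the Quantitative data analysis section gives one rule: "If organizations differ significantly on observable characteristics and baseline outcomes, the model fitting process will use propensity scores". The stated purpose is covariate balancing. The article does not define baseline outcomes, and refers the model equations to Additional file 4, which is not shown here.

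The Measures section defines two outcomes. Penetration is certification reached while grant funding is active. Sustainment is a 10-element score over the five years after funding. Table 1, under "Data collection waves: years since funding ended", puts the first state-focused wave at 4, 3 and 0 years post-funding for cohorts 1, 2 and 3. Interviews with organization-focused grantees were also collected in three waves up to 5 years post-funding.

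The abstract gives the sample as about "85 organizations in 19 states" and "82 organizations in 26 states". The Treatment organizations section describes the earlier data as collected "at 78 treatment organizations (across 27 states").

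**The concern.** There are two problems with the rule.

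**The trigger.** Different agencies, award mechanisms and periods produced the two groups, so imbalance is expected by design and there is no null hypothesis of balance to test. How much a covariate biases the comparison depends on the size of its imbalance and on how strongly it predicts the outcome. A p-value measures neither. With about 80 organizations per group, moderate imbalances often fail to reach significance, and the rule then leaves them out of the propensity adjustment. Read literally, the word joining characteristics *and* baseline outcomes narrows the trigger further, because imbalance on characteristics alone might not set it off.

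**The baseline outcomes.** Neither outcome is described as measured before a grant began. Whatever fills this role has already been exposed to grant type. If grant type works, these values will differ for that reason, and the difference would itself decide whether the model is adjusted.

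At stake is the main contrast in Aims 1 and 2. Some confounding may stay in, the choice of model depends on the data and possibly on the effect itself, and part of the effect could be adjusted away if such outcomes were balanced on.

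**Working it through.** **Inputs from the protocol article.** 85 and 82 organizations (abstract). Detectable effects of 0.46 SD for Aim 1, 0.40 SD when covariates explain 20% of the variance, and 0.34 SD for Aim 2 with intra-class correlation up to 0.40 (Statistical power). First-wave timing (Table 1).

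**Assumed inputs.** True imbalances of 0.20–0.40 SD; covariate–outcome correlations of 0.3–0.5, with √0.20 = 0.447 as the worked value; correlations of 0.2–0.6 between first and later sustainment scores.

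**1. The plan's own figure, for scale.** Without clustering, the detectable effect at 80% power is (1.96 + 0.842) × √(1/85 + 1/82) = 2.80 × 0.155 = 0.43 SD. An effect of 0.46 SD has 84% power, which agrees with the stated power above 80%. No stated figure is in dispute.

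**2. How often the trigger fires for one covariate.** SE of a standardized difference = √(1/85 + 1/82) = 0.155. P(flagged) = Φ(d/SE − 1.96) + Φ(−d/SE − 1.96).

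| True imbalance d | Flagged | Missed |
|---|---|---|
| 0.20 SD | 25% | 75% |
| 0.30 SD | 49% | 51% |
| 0.40 SD | 73% | 27% |

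With 78 organizations in place of 82, the SE is 0.157 and the first two flagging rates become 25% and 48%.

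**3. Bias if nothing is adjusted.** Bias = d × correlation.
- d = 0.20: 0.20 × 0.447 = 0.089 SD
- d = 0.30: 0.30 × 0.447 = 0.134 SD

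That is 19–29% of 0.46 SD (0.089/0.46, 0.134/0.46) and 26–39% of 0.34 SD.

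**4. Bias averaged over the rule.** This is smaller than step 3 for two reasons: the rule sometimes adjusts, and samples that escape the test have smaller observed imbalances. Missed samples are those with an observed imbalance within ±1.96 × 0.155 = ±0.303 SD. The mean of that truncated normal is 0.134 SD for d = 0.20 and 0.179 SD for d = 0.30. At correlation 0.447:
- d = 0.20: bias when missed 0.134 × 0.447 = 0.060; averaged over the rule 0.747 × 0.060 = 0.045 SD
- d = 0.30: bias when missed 0.179 × 0.447 = 0.080; averaged 0.509 × 0.080 = 0.041 SD

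A simulation (6,000 runs per setting, one covariate, regression adjustment standing in for a propensity score, d = 0.2–0.4, correlation 0.3–0.5) gave mean bias of 0.02–0.05 SD and type I error of 5.2–6.2%. Always adjusting gave type I error of 4.6–5.3%.

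**5. Is any outcome pre-exposure?** Penetration is measured during the grant, sustainment after it. In the state-focused sample, cohorts 1 and 2 have 37 + 33 = 70 of 91 organizations (77%) first measured 3–4 years post-funding. The other 21 (23%) are first measured at 0 years. None is measured before award.

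**6. If a first post-grant score were conditioned on.** For a constant effect δ and correlation ρ between first and later scores, the effect left is δ(1 − ρ). With δ = 0.34:
- ρ = 0.2: 0.34 × 0.8 = 0.27 SD
- ρ = 0.4: 0.34 × 0.6 = 0.20 SD, so 40% is removed
- ρ = 0.6: 0.34 × 0.4 = 0.14 SD

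**The case against.** **Baseline outcomes are named only in the trigger.** This stands. A reader might infer that the plan puts post-grant outcomes into the propensity score and so removes the effect Aim 2 seeks. The article does not say so, and the equations are not shown. Even if it did, step 6 shows attenuation, not removal. The trigger problem remains on the narrower reading.

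**The 20% figure belongs to covariates already modelled.** In the Statistical power section it lowers the Aim 1 detectable effect, which implies that those covariates are in the model whatever the trigger does. It also refers to covariates jointly and to penetration only. This stands: the correlation of 0.447 is therefore an assumption here, not the plan's estimate of unadjusted confounding, and 0.09–0.13 SD is a worst case.

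**Several covariates could fire the trigger.** If significance on any one is enough, five independent covariates each imbalanced by 0.20 SD would fire it 1 − 0.75⁵ = 76% of the time, and at 0.30 SD 1 − 0.51⁵ = 97%. That is fair, but the article does not say that any one suffices. If adjustment is likely anyway, the trigger gains nothing.

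**No causal claim is made, and there are sensitivity analyses.** The article disclaims isolating a causal impact, but still hypothesises better results under state-focused grants and speaks of estimating grant type effects. The sensitivity analyses address secular trends, including calendar period, but not imbalance between organizations.

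**Invalid intervals.** A reader might infer that pre-testing makes the reported intervals unusable. The simulated type I error of 5.2–6.2% shows only a slight departure for one confounder.

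**Conclusion.** The concern holds in a limited form. The significance trigger is stated outright and is a poor rule for this design: for a single covariate at 85 versus 82 organizations, it misses a 0.30 SD imbalance about half the time. The average harm from one confounder is modest, about 0.02–0.05 SD. The 0.09–0.13 SD figure applies only if no adjustment of any kind is made for that covariate. Several confounders acting in the same direction would do more harm.

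That every described outcome is post-exposure follows from the article's own definitions. The consequence that can be asserted is that a real grant effect could help decide which model is fitted. Loss of part of the effect, about 40% at correlation 0.40 and 20–60% across 0.2–0.6, depends on outcomes entering the score, which needs clarification.

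The imbalances and correlations are assumptions; the article gives neither. The change should be made, but nothing here shows that the study's conclusions would be overturned.

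**What to change.** - Adjust for confounders in every primary model for Aims 1 and 2, with no significance condition.
- Build the propensity score, or the covariate set, from a pre-specified list of organization and state characteristics dated before each award.
- Assess balance with standardized differences before and after adjustment, not with p-values.
- Remove post-award outcomes from both the trigger and the score. If baseline outcomes was meant to denote pre-grant measures, name them and their source.

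**Cost.** Mostly analysis-plan wording plus some data work. The treatment services survey already planned as a source (N-SSATS) has been annual since 2000, so pre-award years exist for both groups. Planned collection starts in 2009, however. Taking the year before award, 2006–2010 awards need 2005–2009, so collection must be extended back for all but the 2010 awards. Because awards are staggered, the pre-award year differs by cohort. Statistically, the price is a few degrees of freedom and some variability in the weights.
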